## Abstract

**Background:**

Approximately half of 7-year-old children do not meet physical activity (PA) recommendations. Interventions targeting primary school children’s afterschool discretionary time could increase PA. Teaching assistants (TAs) are a school resource and could be trained to deliver after-school PA programmes. Building on earlier work, this paper describes the protocol for a cluster randomised feasibility study of a teaching assistant-led after-school intervention aimed at increasing PA levels of year 4 and 5 children (8–10 years old).

**Methods:**

Phase 1—pre-baseline: 12 schools will be recruited. In all schools, self-reported PA will be measured in all consenting year 3 and 4 children. In four schools, pupils will additionally wear a waist-worn Actigraph accelerometer for 7 days.

Phase 2—baseline: schools will be randomised to one of two enhanced recruitment strategies being tested for children: (1) a club briefing and (2) the briefing plus a taster Action 3:30 session. Up to 30 children per school will be able to attend Action 3:30 sessions and will provide baseline data on height, weight, psychosocial variables and accelerometer-measured PA.

Phase 3—intervention and follow-up: Schools randomised into intervention or control arm. Intervention schools (*n* = 6) will receive a 15-week after-school programme when children are in years 4 and 5, run by TAs who have attended a 25-h Action 3:30 training programme. Control schools (*n* = 6) will continue with normal practice. Follow-up measures will be a repeat of baseline measures at the end of the 15-week intervention.

Phase 4—process evaluation: session attendance, perceived enjoyment and perceived exertion will be assessed during the intervention, as well as the economic impact on schools. Post-study qualitative assessments with TAs, school contacts and pupils will identify how the programme could be refined. Accelerometer-determined minutes of moderate-to-vigorous physical activity (MVPA) per day will be calculated as this is likely to be the primary outcome in a future definitive trial.

**Discussion:**

The Action 3:30 cluster randomised feasibility trial will assess the public health potential of this intervention approach and provide the information necessary to progress to a definitive cluster randomised controlled trial.

**Trial registration:**

ISRCTN34001941. Registered 01/12/2016.

## Background

Physical activity has been shown to reduce the adult risk of heart disease, stroke, type 2 diabetes mellitus, some cancers and obesity and is associated with higher levels of mental well-being [1]. Physical activity in childhood is also associated with lower levels of a number of risk factors, including insulin, glucose, blood pressure and body composition [2], and with improved emotional well-being and self-esteem [3]. Despite the benefits of regular physical activity, objectively measured UK physical activity data show that 51% of 7-year-olds do not met the recommendation of an hour of moderate-to-vigorous intensity physical activity (MVPA) per day [4]. Whilst physical activity during childhood has been shown to moderately track into adulthood [5], physical activity levels typically decline with age [6], with the end of primary school being a key period of decline [7]. Stimulating children’s interest in, and increasing their feelings of competence in relation to, being physically active at this point could ameliorate this decline.

Schools provide opportunities to implement public health interventions to large numbers of children [8]; however, physical activity during the primary school curriculum is limited to 2 h of physical education (PE) per week. As a result, the school curriculum provides restricted opportunities for children to meet PA guidelines or develop their physical skills adequately during this key period of motor coordination and skill acquisition. Therefore, extending and maximising the quality of the current provision is likely to be a cost-effective means of increasing physical activity [9].

Time after-school is a key period that could be utilised to promote physical activity [10]. Children who are inactive after school are less likely to meet physical activity guidelines [11]; therefore, maximising the activity opportunities after-school could be an effective means of increasing physical activity in primary school children [8, 12]. Many children already participate in extra-curricular programmes for additional academic support, music, art-based activities and competitive sports [13]. Provision may be enhanced by the UK government announcement in the 2016 Budget that the primary school PE premium (which often funds after-school programmes) will be doubled to £320 million from September 2017 [14]. However, current extra-curricular provision is dominated by fee-paying provision from external practitioners, such as football coaches [15]. In the current economic climate, more cost-effective means of delivering these programmes, such as the use of existing school staff, are required.

Teaching assistants (TAs) support schools and students in many ways. Many TAs would welcome an opportunity to deliver after-school activities but lack the skills and confidence to do so. Head-teachers are keen to allow TAs to deliver after-school activities because (a) it is consistent with the Extended Schools and NICE guidance [16]; (b) commercial activity session providers are expensive [15]; and (c) it shows that the school is developing the skills of its workforce. Training TAs is an intervention approach which, if shown to be effective, could be rolled out nationwide and could be sustainable within existing school systems.

We recently completed an evaluation of the original Action 3:30 afterschool intervention [12]. The original feasibility study was conducted in 20 schools and participants were Year 5 and 6 pupils (9 to 11 year olds). Results showed that the Action 3:30 intervention could be implemented as planned, was liked by schools, children and TAs, and holds promise as a scalable physical activity approach [17, 18]. The adjusted difference in weekday MVPA at the end of the intervention was 4.3 min higher (95% CI = − 2.6 to 11.3) in the intervention arm. Exploratory, analyses indicated that the original intervention may hold more promise to increase boys’ activity (8.6 min, 95% CI = 2.8 to 14.5) than girls’ (0.15 min, 95% CI = − 9.7 to 10.0). The effect on mean levels of MVPA among boys is among the best that have been shown for physical activity interventions in children [19]. However, more work is needed to improve the content for girls, recruit less active participants, improve attendance and increase the TAs’ ability to manage disruptive behaviour [17, 18].

The aim of this study is to test the feasibility of the revised version of Action 3:30 which has been reworked to more successfully appeal to and engage girls and recruit less active children. Specifically, we have the following objectives:Objective 1: Optimise the intervention to increase activity in boys and girls.Objective 2: Identify effective means of recruiting low-active children.Objective 3: Assess intervention fidelity.Objective 4: Estimate the effect of allocation to the Action 3:30 intervention on weekday MVPA of participants and related physical activity behaviours.Objective 5: Collect the information needed to assess the feasibility of conducting a definitive trial and assess the implementation potential of the intervention.Objective 6: Assess whether progression criteria for conducting a definitive trial are met (see below).

## Methods

### Study design

Action 3:30 is a cluster randomised feasibility trial with school as the unit of allocation. Twelve schools will be recruited, with eight primary schools from South Gloucestershire local authority and four from North Somerset local authority. Schools will be recruited to provide variation in school size and the percentage of pupils eligible for free school meals (an indicator of deprivation). Participants will be pupils who are in years 3/4 (aged 7–9) at the baseline assessment in each of the schools. Data will be collected at two time-points: baseline (T0) which will take place between May and July 2017 and then during the last 6 intervention sessions (T1) which will be in February of the next academic year, meaning pupils will be in years 4/5 (aged 8–10) during the intervention and T1 data collection. The study design also includes an opt-out phase (phase 1) which will occur prior to T0 and will be used to compare the activity levels of children who consent to join the study compared to the overall sample of eligible children. Each of these phases is outlined below.

#### Phase 1: opt-out phase (pre-baseline)

All children in years 3 and 4 in the 12 study schools will be asked to complete the Physical Activity Questionnaire for Older Children (PAQ-C) scale [20] prior to the main study commencing. In four South Gloucestershire schools, children will also be asked to wear an accelerometer for 7 days. Opt-out parental consent will be used. This will allow for analysis of differences in physical activity levels between those who are recruited to phase 2.

#### Phase 2: baseline (T0)

##### Recruitment

We aim to recruit 30 year 3/4 pupils from each school. As girls are less active than boys [21], we will aim for a minimum of 40% of the sample to be girls. All year 3 and 4 children able to regularly take part in physical education lessons will be eligible. In schools where more than 30 children consent, 30 will be randomly selected for the study.

Two methods will be trialled for phase 2 recruitment: briefing (recruitment method A) or briefing plus taster session (recruitment method B). A goal of this project is to examine which of the two approaches is most effective for recruitment, to inform a recruitment strategy in a definitive future trial. Recruitment method A will involve a short briefing in each class to explain the study and provision of student information sheets and parental study information (information sheet and parental consent form to return). Recruitment method B will involve the briefing plus a taster session. Taster sessions will be led by coaches from Bristol City Council (a collaborating partner) and will involve a 20–30-min activity session like that of the Action 3:30 after-school club. Four schools in South Gloucestershire and two in North Somerset will be randomly selected to receive the taster sessions. Written parental consent will be obtained for all participants [22]. A brief questionnaire will be sent home to parents who do not give consent for the main study to assess the reasons for not wanting their child to take part.

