### Analysis plan

#### Quantitative analysis

The main analysis will focus on data relating to characteristics of the sample, recruitment, retention and Action 3:30 session attendance rates, levels of data provision using appropriate descriptive statistics (M, SD, Median, N & %). Evidence of promise of the intervention (i.e., estimates of the potential effect of the intervention on weekday MVPA) will be estimated using random-effects linear regression models adjusting for intervention group, local authority, and baseline MVPA with a focus on 95% confidence intervals with exploratory subgroup analyses by child gender. We will also examine the physical activity profile of children who did not attend the Action 3:30 sessions to assess whether their baseline physical activity levels were different to children who attended.

Secondary analysis will pilot the use of a complier average causal effect (CACE) analysis [33] for the four schools that used the “accelerometer opt-out” consent procedure. This model will examine the effect of receiving Action 3:30 on MVPA (original recruits and late joiners) when compared to the control arm and will provide an indication of the overall benefits of the study for all participants who were exposed to Action 3:30 as part of the original sample and late joiners.

Potential sample sizes for a future definitive trial will be estimated using the derived intraclass correlation coefficient (ICC) for MVPA from this study and published ICCs from comparable studies, the target differences in MVPA, and combinations of key parameters (type I and type II error).

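### The goal of finding the more effective recruitment method has no matching analysis: recruitment data are only described, with no school-level B minus A difference or interval

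*Protocol article*

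**What the plan says.** Under Recruitment (Phase 2), the protocol article sets up the comparison: "Two methods will be trialled for phase 2 recruitment: briefing (recruitment method A) or briefing plus taster session (recruitment method B"). Its purpose is stated there too: "A goal of this project is to examine which of the two approaches is most effective for recruitment", so that the answer can guide recruitment in a future definitive trial. Allocation is random within local authority: "Four schools in South Gloucestershire and two in North Somerset will be randomly selected to receive the taster sessions". Study design gives the total: "Twelve schools will be recruited, with eight primary schools from South Gloucestershire local authority and four from North Somerset local authority".

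Under Quantitative analysis, recruitment falls within one general sentence. The main analysis is to cover sample characteristics and "recruitment, retention and Action 3:30 session attendance rates, levels of data provision using appropriate descriptive statistics (M, SD, Median, N" and %). The same paragraph treats the intervention effect on weekday MVPA differently; it "will be estimated using random-effects linear regression models adjusting for intervention group, local authority, and baseline MVPA with a focus on 95% confidence intervals".

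Table 1 lists the opt-in percentage, in total and by sex, with no contrast by method. None of the five progression criteria compares A with B. Other planned evidence on recruitment is a questionnaire to parents who do not consent, and interviews and focus groups that cover factors affecting recruitment.

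**The concern.** Asking which of two randomised methods recruits better is a comparative question, and the answer is meant to feed the design of the definitive trial. Summaries by method do not by themselves answer it. The unit randomised is the school, so the uncertainty in the difference comes mainly from how much consent varies between schools. Two percentages calculated over pupils hide that. The article does recognise clustering and asks for an interval when it turns to MVPA, but does neither for this second randomised comparison.

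At stake is the recruitment strategy of the definitive trial. Method B adds a coach-led session to the briefing. If a chance difference between six schools and six schools is read as a difference between methods, the taster could be carried forward for no gain, or a real gain could be overlooked.

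**Working it through.** **Design check.** Method B goes to 4 + 2 = 6 schools. Of 8 + 4 = 12 schools, 6 remain for A. The article gives no sample size, margin or expected difference for A v B, so there is no planned figure to reproduce.

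**Inputs.**
- Schools per method: 6 (article).
- Consent proportion p: 0.25, the level in the second progression criterion; 0.40 as a sensitivity value (assumption).
- Eligible pupils per school m: 60, 90, 120 (assumption).
- ICC of consent between schools: 0.02, 0.05, 0.10, with 0 as a lower bound (assumption).

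**Standard error of the difference in mean school proportions.**

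SE = sqrt[(2/6) × p(1 − p)/m × (1 + (m − 1) × ICC)]

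For m = 120 and p = 0.25, p(1 − p)/m = 0.1875/120 = 0.0015625.
- ICC 0.02: sqrt(0.0015625 × 3.38/3) = 0.042
- ICC 0.05: sqrt(0.0015625 × 6.95/3) = 0.060
- ICC 0.10: sqrt(0.0015625 × 12.9/3) = 0.082

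**Half-width of the 95% interval.** With 12 schools in two groups there are 10 degrees of freedom and t = 2.228, so for m = 120 the half-widths are 9.3, 13.4 and 18.3 points. Adjusting for local authority leaves 9 degrees of freedom (t = 2.262), a change of 1.5%.

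**Apparent gaps when the methods are identical.** These come from 100,000 simulated trials per row, with beta-binomial consent counts, 6 v 6 schools and p = 0.25. The local-authority strata were ignored.

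| m | ICC | SE (points) | 95% half-width (points) | Gap ≥ 5 points | Gap ≥ 10 points |
|---|---|---|---|---|---|
| 60 | 0.02 | 4.8 | 10.6 | 31% | 4% |
| 60 | 0.05 | 6.4 | 14.3 | 45% | 13% |
| 60 | 0.10 | 8.5 | 18.9 | 57% | 24% |
| 90 | 0.02 | 4.4 | 9.8 | 26% | 2% |
| 90 | 0.05 | 6.2 | 13.7 | 43% | 11% |
| 90 | 0.10 | 8.3 | 18.5 | 56% | 23% |
| 120 | 0.02 | 4.2 | 9.3 | 24% | 2% |
| 120 | 0.05 | 6.0 | 13.4 | 41% | 10% |
| 120 | 0.10 | 8.2 | 18.3 | 55% | 23% |

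The normal approximation for the m = 120, ICC 0.02 row gives 23%, the lower end of the range quoted.

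**Sensitivity.** With ICC 0, gaps of 5 points or more arise in 13%, 6% and 3% of trials for m = 60, 90 and 120, so the size of the problem depends on real variation between schools. At 40% consent with ICC 0.02 to 0.10, the ranges are 30% to 61% for 5 points and 4% to 30% for 10 points.

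**Why the school must be the unit.** Under identical methods (p = 0.25, ICC 0.02 to 0.10), a pupil-level test that ignores schools would be significant at the 5% level in 19% to 59% of trials. The school-level t comparison stays at about 5% in every row. The article does not propose the pupil-level test; the contrast shows what ignoring the cluster would cost.

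**What 12 schools can detect.** (t for 97.5% + t for 80%, 10 df) × SE gives about 13 to 26 points for 80% power over the same range.

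**The case against.** The strongest reply is that the article promises little. It speaks of examining the methods and informing a strategy, in a feasibility study, where descriptive reporting is normal. The sentence on descriptive statistics covers recruitment data in general and never describes the A v B comparison. An unseen analysis plan or full protocol may hold a model and an interval. If means and SDs were reported by method at school level, a reader could derive a standard error. Qualitative evidence on recruitment is planned as well.

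Much of this stands. A reader might infer that the method with the higher percentage will be adopted, so that a winner is declared even when the methods are equal. The documents do not support that: no such rule appears, no progression criterion compares the methods, and some difference between two noisy estimates is no defect in itself. Nor can it be said that descriptive percentages will be the only evidence used.

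The mismatch remains. The article is not silent on recruitment data: it assigns them to description, and in the same paragraph gives MVPA a clustered model and an interval. It does not say that the means and SDs will be taken over schools or split by method. The goal is also not tied to a measure: Table 1 names the opt-in percentage, whereas Objective 2 concerns low-active children.

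**Conclusion.** The point holds as a mismatch between goal and stated analysis. A randomised 6 v 6 comparison is asked which method recruits best, and the only quantitative analysis stated for recruitment data gives no contrast, no interval and no account of the school as randomised unit. At 25% consent, 60 to 120 eligible pupils per school and an ICC of 0.02 to 0.10, equal methods would show a gap of at least 5 points in roughly 23% to 57% of trials, and a proper interval would have a half-width of roughly 9 to 19 points. School size and ICC are assumptions, and the figures shrink if schools vary little.

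A reader might also infer that a significance test would settle the choice. It would not, because only differences of about 13 to 26 points are detectable with 80% power. The consequence is limited to the recruitment conclusion; the MVPA estimate is unaffected.

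**What to change.** In Quantitative analysis, state that methods A and B are compared on the school-level proportion of eligible year 3/4 pupils returning consent. Report the B minus A difference from the 12 school proportions, adjusted for local authority (within which the method was allocated), with a t-based 95% confidence interval. Under Recruitment, reword the goal as estimating this difference, to be read with the parent questionnaire, interviews and focus groups, and not as selecting the most effective method.

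Do not add a rule that adopts B once its point estimate reaches a threshold. Such a rule ignores the interval. With a 5-point threshold it would adopt B under no true difference in about 12% to 28% of trials (half of 24% to 57%), and it would miss a true gain equal to the threshold about half the time.

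The cost is a few lines of text and one small regression on data already being collected. The downside is that the interval will be wide, and the report may have to say that the methods were not separated.

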##### Measures

All measures will be taken at baseline (T0) prior to randomisation and again during the last six intervention sessions (T1) and will be conducted by trained members of the research team. At both time points, children will wear an ActiGraph accelerometer for seven consecutive days to assess physical activity levels. The raw accelerometer data will be integrated into 10-s intervals at point of download. Periods of ≥ 60 min of zero counts will be recorded as “non-wear time” and removed. Children will be included in analysis if they provide ≥ 3 valid days (500 min of data between 6 a.m. and 11 p.m.). Minutes in MVPA will be established for weekdays and weekends, using cut-points developed for children [23]. Accelerometer counts per minute (cpm), an indication of the volume of total activity, will also be derived. Sedentary time will also be estimated based on a cut-point of less than 100 cpm. MVPA and total activity will also be assessed during the period after-school.

At each time point, children will complete a questionnaire assessing activity-based perceptions of autonomy, relatedness, competence and enjoyment using established scales. Children will also complete the KIDSCREEN-10 [24] and Child Utility 9D [25] (CHU9D) questionnaires to assess health-related quality of life. These questionnaires will be completed on tablet devices to aid data completion.

Children’s height and weight will be measured to the nearest 0.1 cm with their shoes, coats and jumpers removed, using a portable SECA stadiometer and digital SECA scale, respectively. Body mass index (kg/m^2^) will be calculated and converted to an age- and sex-specific body mass index standard deviation score [26].

Data on socioeconomic status and ethnicity of child will be collected via parental questionnaire sent home at T0. Mode of travel to and from school will also be assessed via the parental questionnaire at T0 and T1.

The schedule for recruitment and proposed study measures are outlined in the SPIRIT diagram displayed in Table 1 and in the Consolidated Standards of Reporting Trials (CONSORT) diagram (Fig. 1).

**Table 1 Tab1:** Action 3:30 SPIRIT diagram displaying study recruitment and measures schedule

	Study period				
	Pre-enrolment	Enrolment	Allocation	Post-allocation	Follow-up
Timepoint	Opt-out	T0	Randomization	Intervention	T1
Enrolment					
Opt-out consent	X				
Opt-out survey (12 schools)	X				
Opt-out accelerometer (4 schools)	X				X
Informed parental consent		X			
Baseline measures		X			
Randomization into study arm			X		
Interventions					
TA training (intervention schools)				X	
Extracurricular physical activity intervention (6 schools)				X	
Normal treatment (6 schools)				X	
Assessments					
Percentage opt-out	X				X
Self-reported physical activity	X				
Percentage opt-in (total, by sex)		X			
Participant characteristics		X			X
Self-reported psychosocial questionnaires		X			X
Economic evaluation				X	X
Mean daily moderate-to-vigorous physical activity		X			X
Process evaluation				X	X

